# Effectiveness of a community-based support programme to reduce social inequality in exclusive breastfeeding: study protocol for a cluster-randomised trial

**DOI:** 10.1186/s12889-023-15256-z

**Published:** 2023-03-08

**Keywords:** Breast feeding, Community health, Complex interventions, Cross-sectoral consistency, Delivery of health care, Health care sector, Health visitor, Postnatal care, Randomized controlled trials, Socioeconomic factors

## Abstract

**Background:**

Breastmilk is the ideal nutrition for infants, and breastfeeding protects infants and mothers from a range of adverse health outcomes. In Denmark, most mothers initiate breastfeeding but many cease within the first months resulting in just 14% reaching the World Health Organization recommendation of six months of exclusive breastfeeding. Furthermore, the low breastfeeding proportion at six months is characterised by a marked social inequality. A previous intervention tested in a hospital setting succeeded in increasing the proportion of mothers breastfeeding exclusively at six months. However, most breastfeeding support is provided within the Danish municipality-based health visiting programme. Therefore, the intervention was adapted to fit the health visiting programme and implemented in 21 Danish municipalities. This article reports the study protocol, which will be used to evaluate the adapted intervention.

**Methods:**

The intervention is tested in a cluster-randomised trial at the municipal level. A comprehensive evaluation approach is taken. The effectiveness of the intervention will be evaluated using survey and register data. Primary outcomes are the proportion of women who breastfeed exclusively at four months postpartum and duration of exclusive breastfeeding measured as a continuous outcome. A process evaluation will be completed to evaluate the implementation of the intervention; a realist evaluation will provide an understanding of the mechanisms of change characterising the intervention. Finally, a health economic evaluation will assess the cost-effectiveness and cost-utility of this complex intervention.

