### Objectives

The primary objective of the Breastfeeding Trial is to assess the effect of a community-based breastfeeding support programme delivered by health visitors in primary healthcare on the duration of exclusive breastfeeding and social inequality in breastfeeding among women in Denmark. Our hypothesis is that women who receive strengthened breastfeeding support in conjunction with the breastfeeding support offered in the hospital setting will overcome breastfeeding challenges and therefore breastfeed exclusively for a longer period of time. We anticipate that by administering a higher dose of the intervention to mothers who are young or have a low educational attainment, the effects will be even stronger in this group, thereby reducing social inequality in breastfeeding.

We will conduct a comprehensive, multidisciplinary evaluation of the trial by investigating whether the present complex intervention is effective compared with usual breastfeeding support, with respect to:The proportion of women who are breastfeeding exclusively at four months postpartumThe overall duration of exclusive breastfeedingReducing social inequality in breastfeeding

In a process evaluation, we investigate the processes of implementation, specifically:Facilitators of and barriers to implementing the interventionDose, delivery and fidelity of the interventionHow the training programme affects health visitors’ knowledge, self-efficacy and action competencies regarding breastfeeding support

Using a realist evaluation approach, we investigate the relationship between context, mechanisms and outcomes to determine *whether* and *how* the intervention works. The realist evaluation will focus primarily on families in which the mother is young or holds a low educational attainment (i.e., the group that will receive an intensified version of the intervention (see a description of the intervention in Table 2)). More specifically, we will:Investigate important mechanisms of change by examining families and health visitors’ response to and interaction with the interventionAnalyse how contextual factors promote or inhibit the implementation process and the expected mechanisms of change and the potential consequencesInvestigate how the intervention works for mothers who are at an increased risk of early breastfeeding cessation

Finally, in a health economic evaluation, we will assess:The cost-effectiveness of the interventionThe cost-utility of the intervention

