### Outcome measures of the effectiveness trial

Data on the primary outcome measure of exclusive breastfeeding at four months are collected through a survey. To gain as much insight into the intervention mechanisms and effects as possible, we collect data from various sources as described in the aim. As the trial was designed to show effects on survey-based measures, we elaborate on the survey trial design below and afterwards describe the supplementary data sources.

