#### Primary outcome measure

Proportion of mothers who exclusively breastfeed at four months postpartum.

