#### Secondary outcome measures

The secondary objectives are to assess the effectiveness of the breastfeeding support programme on:Duration of exclusive breastfeeding (continuous)Infant readmissions to hospital related to nutritionMothers’ experiences of breastfeeding problemsParental trust in the health visitorMaternal breastfeeding self-efficacyPaternal feeling of inclusion in the breastfeeding supportBreastfeeding in mothers with overweight

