**Primary**							
Exclusive breastfeeding four months (binary)			X				*NCHR*
Exclusive breastfeeding (continuous)	X	X	X				*NCHR*

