### Statistical methods

We use random allocation to remove any influence of both measured and unmeasured variables on treatment allocation. Before conducting regression analyses, descriptive statistics will be applied to assess selection into the trial, baseline equivalence of trial arms and loss to follow-up.

Regression analyses will be applied when analysing primary outcomes. We will account for the clustered nature of data by using random effects models for binary and continuous outcomes [51] and shared frailty models for analysing time-to-event and recurrent events in continuous outcomes [52]. Intention-to-treat analyses will be conducted. These analyses will include all mother-infant dyads in the relevant trial arms irrespective of their compliance or loss to follow-up. Complete-case analyses will be conducted restricted to observations with available outcome measures [53]. For the intention-to-treat analyses, the survey data will be linked to the Danish national registers including all births; and missing outcome data will be handled by inverse probability weighting and missing covariates by multiple imputation from the registers. The probability weights will be estimated by conducting logistic regressions with outcome data (yes vs. no) as dependent variable and the following baseline variables as predictors: maternal educational, maternal age, cohabitation status, partner’s education, household income, occupational status, maternal smoking status, maternal BMI, and maternal as well as paternal psychiatric histories.

The effect of the intensified intervention will be examined by including an interaction term between treatment arms and a binary indicator of the mother being young or having low educational attainment.

All models will be analysed with treatment alone and adjusted for known predictors for breastfeeding duration collected in the survey (smoking status, maternal age, maternal education, parity, mode of delivery, maternal BMI and cohabitation status) and for design variables used in the randomisation (region of Denmark and number of annual births (< 900 births/year vs. ≥ 900 births/year). As the randomisation will hopefully have distributed the characteristics evenly between trial arms, these adjustments are made to increase the robustness of the effect estimations. Missing predictors will be imputed using multiple imputations and the results compared to the complete case analysis.

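### Continuous duration of exclusive breastfeeding is primary in the abstract and Table 3 but secondary in the outcome section, and the sample size covers only the four-month proportion

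*Protocol article*

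**What the plan says.** Some places in the protocol article treat duration as primary:

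- Abstract, Methods: "Primary outcomes are the proportion of women who breastfeed exclusively at four months postpartum and duration of exclusive breastfeeding measured as a continuous outcome".
- Table 3, primary block: two rows, "Exclusive breastfeeding four months (binary" and "Exclusive breastfeeding (continuous". The continuous row is marked for the survey waves at one week, one month and four months, and for the National Child Health Register.
- Statistical methods uses the plural: "Regression analyses will be applied when analysing primary outcomes".
- Objectives: the primary objective is the effect of the programme "on the duration of exclusive breastfeeding and social inequality in breastfeeding among women in Denmark".

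Other places treat the four-month proportion as the only primary outcome:

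- Outcome measures of the effectiveness trial: "Data on the primary outcome measure of exclusive breastfeeding at four months are collected through a survey". The Survey data section also uses the singular.
- Primary outcome measure, in full: "Proportion of mothers who exclusively breastfeed at four months postpartum".
- Secondary outcome measures: the first item is "Duration of exclusive breastfeeding (continuous".
- Sample size and power calculations: sized on the four-month proportion alone, 49% against 56%, with one 5% significance level, 80% power, ICC 0.001 and eight clusters per arm, giving 111 mothers per cluster. No mean difference, standard deviation or hazard ratio is given for duration.

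**The concern.** The designation of the primary outcome decides what the trial may claim as its confirmatory result. Here the same variable, measured in the same survey, is primary in two places and secondary in another. If the four-month comparison is null and duration is significant, an author could cite the abstract and report success on a primary outcome, or cite the outcome section and report a secondary finding. Prespecification is meant to remove that choice.

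The label also determines whether the stated 5% level and 80% power describe the confirmatory analysis. They do for the four-month proportion as sole primary. They do not automatically carry over to two primary outcomes, and how far they fail to do so depends on the rule for declaring success.

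**Working it through.** **1. Reproducing the sample size.** Inputs from Sample size and power calculations: p1 = 0.49, p2 = 0.56, alpha 0.05 (sidedness is not stated; two-sided reproduces the figure), power 0.80, ICC 0.001, k = 8 clusters per arm.

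- Odds ratio: (0.56/0.44)/(0.49/0.51) = 1.325; the article gives 1.32.
- Per arm before clustering, with pooled variance under the null and no continuity correction: n = [1.960·√(2·0.525·0.475) + 0.842·√(0.49·0.51 + 0.56·0.44)]² / 0.07² = 798 after rounding up.
- With cluster size m, k·m = n·[1 + (m − 1)·ICC], so m = n(1 − ICC)/(k − n·ICC) = 798·0.999/(8 − 0.798) = 110.7, that is 111. This matches.
- Power at 111: the effective size per arm is 8·111/(1 + 110·0.001) = 888/1.11 = 800, which gives 80.1%.
- Subgroup, 45% against 55%: n = 392 per arm and m = 392·0.999/(8 − 0.392) = 51.5, that is 52, with power 80.5%. This also matches.

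The calculation is therefore correct, and it is a calculation for one binary outcome tested once.

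**2. Can the two designations be reconciled?** One might read the abstract as covering the register analysis and the outcome section as covering the survey. Table 3 rules this out, because its continuous primary row is marked for three survey waves as well as the register. The secondary list, too, belongs to the survey section. The two labels conflict for the same survey measure.

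**3. Error rate under each possible success rule.**

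- Four-month proportion as sole primary: 5%.
- Both outcomes must succeed: at most 5%.
- Either outcome at 5% suffices: familywise error = 1 − P(|Z1| < 1.96 and |Z2| < 1.96), with Z1 and Z2 bivariate normal with correlation r. The documents do not give r, so a range is shown.

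| Assumed r | Familywise error |
|---|---|
| 0 | 1 − 0.95² = 9.75% |
| 0.5 | 9.1% |
| 0.7 | 8.3% |
| 0.8 | 7.8% |
| 0.9 | 7.0% |

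Four-month status is essentially a cut-point of duration in the same mothers, so the lower rows are the more realistic.

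**4. Power if both are kept with a Bonferroni split (2.5% each).**

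- Four-month outcome: n = 967 per arm and m = 967·0.999/(8 − 0.967) = 137.4, that is 138 per cluster.
- At 111 per cluster and 8 clusters per arm, power is 71.3%.
- The article reports 21 municipalities, 11 of them intervention, which leaves 10 control. Taking 10 per arm at 111 mothers each as an assumption, the effective size is 1110/1.11 = 1000 per arm, with power 88.0% at 5% and 81.5% at 2.5%.
- Duration: not computable, because no effect size or variability is given.

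**The case against.** The strongest reply is that the operative design text agrees with itself. The outcome section names one primary outcome, the Survey data section uses the singular, and the sample size rests on that outcome at a single 5% level and reproduces exactly. On this view the abstract, one table row and a plural noun are slips of labelling.

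Much of this stands. It identifies which designation the design supports, and it shows that the sample size needs no correction. It does not remove the conflict: Table 3 and Statistical methods are also in the body of the article, and the primary objective names duration, so the wording is not confined to the abstract.

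A reader might infer several stronger things that the documents do not support:

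- That the trial already runs at an error rate above 5%. Inflation needs an either-suffices rule, and the article states none.
- That the inflation is 9.75%. That figure assumes independence, which cannot hold for two such closely related outcomes.
- That duration has no power. Its power is unstated, which is different. With more municipalities enrolled than the 16 assumed, the four-month outcome might keep 80% power even at 2.5%.
- That the absence of an alpha split or testing order is itself an error. This is a condensed article, and such a rule may sit in an analysis plan that is not shown.

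**Conclusion.** The point holds as an internal contradiction about the status of continuous duration: primary in the abstract and Table 3, supported by the plural in Statistical methods and the wording of the primary objective, but secondary in the outcome section. An analysis plan could supply a multiplicity rule, but the conflicting labels would still stand in this article.

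The main consequence is freedom in reporting. The consequence for the error rate is conditional: 5% under a sole primary or a both-must-succeed rule, and about 7.0% to 9.1% under an either-suffices rule at assumed correlations of 0.9 to 0.5. The sample size is sound for the four-month proportion alone. The 71.3% power under a 2.5% test assumes the planned 8 clusters per arm and 111 mothers per cluster, and would be higher with the clusters actually enrolled.

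**What to change.** Before analysis, designate the four-month proportion as the single primary outcome throughout. This fits the outcome section and the sample size. Specifically:

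- move duration to secondary in the abstract and in Table 3;
- use the singular in Statistical methods;
- align the primary objective, which otherwise would have no matching primary outcome;
- test duration for a confirmatory claim only after a significant four-month result.

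Keeping both outcomes as primary is also legitimate. The sponsor would then have to state whether one or both must succeed, give the alpha allocation, restate the power for the four-month outcome at its share of alpha, and add an effect size and power for duration.

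The first option costs only wording, plus a check that the registration and any analysis plan (neither shown here) say the same. It needs no new data and leaves 111 mothers per cluster unchanged. The second may need more mothers: 138 per cluster with 8 clusters per arm under an even split.

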**Discussion:**

This study protocol reports on the design and evaluation of the Breastfeeding Trial – a cluster-randomised trial implemented within the Danish Municipal Health Visiting Programme from April 2022 to October 2023. The purpose of the programme is to streamline breastfeeding support provided across healthcare sectors. The evaluation approach is comprehensive using a multitude of data to analyse the effect of the intervention and inform future efforts to improve breastfeeding for all.

**Trial registration:**

Prospectively registered with Clinical Trials NCT05311631 https://clinicaltrials.gov/ct2/show/NCT05311631

**Supplementary Information:**

The online version contains supplementary material available at 10.1186/s12889-023-15256-z.

## Background

Breast milk is the ideal nutrition for infants. A meta-analysis has demonstrated that breastfeeding protects the infant against infections and malocclusion, increases intelligence and potentially reduces overweight and diabetes later in life [1]. Furthermore, breastfeeding protects the mother against breast cancer and possibly also against ovarian cancer and type 2 diabetes [1]. Thus, few health behaviours have as important public health benefits as breastfeeding given its potential to improve life chances, health and well-being [2]. The World Health Organization (WHO) recommends exclusive breastfeeding of infants in the first six months of life when possible, and partial breastfeeding alongside complementary foods for up to two years of age or beyond [3].

The proportion of women who initiate breastfeeding in Denmark is among the highest in the world [4] with more than 97% initiating breastfeeding [4, 5]. Yet, in recent years, the proportion of Danish women breastfeeding exclusively for six months has reached no more than 14% [6]. In line with the WHO, the Danish Health Authority recommends six months of exclusive breastfeeding, simultaneously recommending that solids is not introduced to the infant’s food before the age of four months [7]. Consequently, Danish exclusive breastfeeding rates drop markedly around four months after birth [8].

A social gradient in breastfeeding has been documented in high-income countries [4, 9, 10] including Denmark [11]. Young mothers and mothers with a low socioeconomic position (SEP) are the least likely to initiate breastfeeding and most likely to cease breastfeeding before six months [12, 13]. However, a recent study found that after adjusting for psychosocial factors such as breastfeeding self-efficacy and sense-of-security, education no longer had a prognostic effect on the duration of exclusive breastfeeding [14], implying that efforts to underpin self-efficacy and sense-of-security may reduce the social gradient. Previous research has found that early breastfeeding cessation is frequently due to a perceived insufficient milk supply [15–17] and that mothers at risk of early breastfeeding cessation require more support from healthcare providers to achieve their breastfeeding goals [2]. Consistency in breastfeeding support information is important for mothers in general and for young mothers in particular [18]. Furthermore, young mothers frequently require more specific support in the form of affirmation and recognition of their efforts, which boosts their self-efficacy and motivation [18–22]. The timing and frequency of the support given are important, but evidence is insufficient to recommend a specific schedule [23].

In Denmark, breastfeeding support is initiated immediately after giving birth in the maternity ward setting. After hospital discharge, breastfeeding support is continued in the families’ homes within the context of a universal, municipality-based and tax-financed health visiting programme [24]. Danish health visitors are registered nurses with a minimum of three years of full-time clinical experience and an additional 1.5 years of training [25]. With early discharge following birth, most breastfeeding support is provided by the health visitors. Challenges relating to inconsistency in breastfeeding recommendations and cross-sector breastfeeding support have been experienced by women [26].

In 2013–14, Nilsson et al. (2017) implemented a breastfeeding support programme in a hospital setting for mother-infant dyads facing early discharge [27]. When compared with usual care, the intervention improved exclusive breastfeeding at six months postpartum and reduced infants’ readmissions to hospital within the first week of life [27]. The intervention included training of healthcare professionals in providing improved breastfeeding support, aiming to increase mothers’ breastfeeding self-efficacy by simplifying breastfeeding counselling to four key principles: 1) Skin-to-skin contact, 2) Frequent breastfeeding, 3) Proper positioning and 4) Joint parenting task [27]. Subsequently, these principles were included in the breastfeeding recommendations of the Danish Health Authority [7] and either partially or completely implemented throughout Danish maternity wards.

Knowing that the previous intervention was effective, that cross-sector breastfeeding inconsistencies exist, that most breastfeeding support is provided following discharge with an estimated 97% of parents accepting the health visiting programme [28] and that a social gradient in breastfeeding exists, we decided to develop the ‘Breastfeeding – A Good Start Together’ trial (henceforth termed The Breastfeeding Trial). Our ambition was to strengthen breastfeeding support offered within the municipality-based health visiting programme and to align it with the dominating current practice in the hospital setting. The aim of the intervention was to raise exclusive breastfeeding rates and reduce social inequality in breastfeeding.

Prior to adapting the intervention from use in a hospital setting to use in the health visiting programme, we identified important knowledge gaps. A narrative literature review revealed that mothers who were young or had a low educational attainment frequently wished and intended to breastfeed but found themselves overwhelmed by their birth, the transition into motherhood and various breastfeeding challenges. These complexities meant that they had a lower threshold for giving up breastfeeding [29]. They also struggled with embarrassment related to breastfeeding and were easily influenced by attitudes in and experiences with breastfeeding in their social networks [29]. A qualitative study identified the early period after discharge as an especially vulnerable period. During this period, e.g., the stability, self-efficacy, sense of stigma towards age and breastfeeding attitude in families would potentially make them opt out of breastfeeding [30]. The families experienced a need for basic, practical knowledge and visual information; they found such information online or purchased help from private lactation consultants. However, a positive relationship with the health visitor was highlighted as essential to parents’ benefit from breastfeeding support [30].

As social inequality in breastfeeding may contribute to persistent health inequities across generations [31], interventions to increase breastfeeding are an important public health matter. Previous research call for future breastfeeding interventions exploring how support may best be provided consistently, and describe in detail the attributes of the intervention, standard care and the population group studied to provide strong evidence for future reference [2]. The goal of this study protocol is to describe the Breastfeeding Trial and the standard care provided, while outlining plans and methods for analysing effects and describing other pertinent evaluation techniques.

